### Participants

We will conduct experiments in parallel at the School of Psychology and Neuroscience, University of Glasgow (Glasgow, Scotland) and at York University (Toronto, Canada). We will share programming scripts and methodology between sites.

In these experiments, we will test neurotypical subjects with normal or corrected to normal vision. We will only include participants with corrected to normal vision in cases where calibration works reliably (correction lenses sometimes reflect infra-red light, which can disturb eye tracking).

We will recruit participants through each site’s internal recruitment system. Participants give written consent. Participants in Glasgow will be reimbursed for their time at a rate of £7/h; participants in York will be reimbursed at a comparable rate in CA$20 or course credit. Each site’s human research ethics committees have granted ethical approval for this project (College of Science and Engineering Ethics Committee, University of Glasgow – Application Number: 300200313; Toronto – York University’s Human Participants Review Committee, Certificate e2019-194).

We will assess the presence of space distortions on perceived distance, area size and motion trajectories in areas neighbouring participants’ blind spot region. The use of small dot stimuli to study spatial vision near the blind spot has precedent (e.g., [20]). We hypothesise that effects might be small, so we will use a larger sample size (32 participants per experiment) than typical studies of perception across the blind spot (e.g., [3,20,24,25]).

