We will show both target and foil for each trial either to the ipsilateral or contralateral eye. Crucially, while the foil dot pair will never span the blind spot (presented half the time above or below in a randomised order within a staircase), we will show the target dot pair either spanning the blind spot or not. For each of these combinations, we will define 2 staircases, one for which the foil distance starts as the smallest possible value (i.e., obviously smaller than the target distance) and one for which it starts at the largest possible value (i.e., obviously larger than the target distance). This yields a total of 8 staircases (2 eyes x 2 starting differences x 2 target pair locations) that will run interlaced to compose one run. One staircase procedure ends when it has lasted for at least 30 trials, and there have been at least 10 reversals (defined as a switch from choosing the foil to choosing the target or the opposite). At the start of each trial, one of the staircases that has not already finished will be randomly selected until all staircases are done. A full session of this task including calibration and two runs lasts approximately one hour and a half.

Using these data, we will model psychometric functions relating distance difference between target and foil to the proportion of times the target is chosen as being smaller in distance. These functions will be allowed to vary in terms of bias and precision according to the experimental conditions (around vs not around the blind spot, ipsilateral vs contralateral eye), making it possible to quantify potential disruption of distance perception induced by the blind spot.

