### Planned analyses and expected outcomes

Using the data from task 1, we will model the psychometric functions relating the distance difference between target and foil to the proportion of trials the target is chosen as being the smaller distance. Using the data from task 2, we will model the distribution of perceptual area size equivalence across trials. Using the data from task 3, we will model the psychometric functions relating apparent motion curvatures to the proportion of times they are chosen as being curved away from fixation. The resulting models, fitted using a probit link function, will be allowed to vary in terms of intercept (capturing bias effects) and slope (capturing precision effects) according to the experimental conditions (around vs not around the blind spot, ipsilateral vs contralateral eye). Thus, our modelling approach will quantify the potential disruption of spatial perception induced by the blind spot as bias and precision effects for either the ipsilateral or contralateral eye. This modelling approach will be implemented in two ways. We initially use a linear mixed effects model (lme4 package in Rstudio; see [29]), which includes random intercepts for participant and hemifield in addition to the fixed effects of our experimental conditions. This has allowed us to get a first estimate of the effect of eye (ipsilateral eye vs contralateral eye) or location (nearing vs away from blind spot) on the bias and precision of spatial perception while accounting for participant and hemifield response variability.

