## Discussion

This study protocol forms one of four protocols (to be published separately) that were designed in an adversarial collaboration (Intrepid project) between information integration theory (IIT; [5]), and two branches of predictive processing, active inference (AI; [6,7]) and neurorepresentationalism (NREP; [8,9,15]). In the context of our study, the theories made differential predictions on the behavioural effects that the un-stimulated blind spot region may have on judgements of distance, area, and motion curvature. We will use these behavioural effects to assess the different theoretical predictions of the three theories (see Fig 6 for simulated data of each theory’s predictions). This will be done first through standard linear mixed-effects modelling, followed by a Bayesian analysis applied both within our protocol and across the broader collaborative framework, aiming to better understand the mechanisms behind the conscious experience of space.

Among the challenges that may affect our ability to arbitrate between the theoretical accounts and our observed data is, firstly, the fact that although the different theories predicted the direction of the effect on space, they did not specify the magnitude. For example, NREP argued that ‘small’ (down to ‘non-existent’) spatial disruptions could take place when judgements involved the un-stimulated blind spot region, where ‘small’ means a modest effect that is nonetheless significant (p < 0.05 according to frequentist statistics). Conversely, IIT proposed that space should be perceived as smaller around the blind spot region, but did not define how much of a disruption would be theoretically relevant.

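### The first-stage mixed model has random intercepts only, so the location and eye contrasts are tested against trial noise and not against differences between participants

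*Protocol article*

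**What the plan says.** Under Planned analyses and expected outcomes, the fitted functions "will be allowed to vary in terms of intercept (capturing bias effects) and slope (capturing precision effects) according to the experimental conditions". The first implementation is a mixed model in lme4 that "includes random intercepts for participant and hemifield in addition to the fixed effects of our experimental conditions". The section says this estimates the eye and location effects on bias and precision "while accounting for participant and hemifield response variability". No variation between participants in the condition effects is mentioned anywhere.

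The design crosses location and eye within each person. The distance task runs "a total of 8 staircases (2 eyes x 2 starting differences x 2 target pair locations"), and the area task repeats its adjustments for each eye, location and hemifield. The sample is "32 participants per experiment", chosen because effects may be small.

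The Discussion makes the mixed model the first step in assessing the theories. It describes NREP's small effect as "a modest effect that is nonetheless significant (p < 0.05 according to frequentist statistics"). A Bayesian model comparison follows. Planned analyses says that with neutral priors it will recover the same general bias and precision effects.

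**The concern.** A random intercept for participant absorbs a person's overall level of responding, but that level already cancels in a contrast made within the person. It does not absorb differences between people in the contrast itself. If one person shows some compression across the blind spot and another shows some expansion, that spread belongs in the standard error of the mean effect. The stated model has no term to carry it, so the trials act as the independent units, not the 32 people. The claim that participant variability is accounted for holds for response level but not for the effects that test the theories.

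Some spread is plausible. Target distance, circle diameter and trace position are all set from each participant's own mapped blind spot.

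Table 1 is read from these contrasts. AI predicts no bias effect, while IIT predicts a decrease and NREP allows one. A standard error that is too small can turn a chance average of individual differences into a significant bias.

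**Working it through.** The plan gives no power or error-rate figure to reproduce, so the check asks what the stated model does when the mean effect is zero.

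**Inputs from the protocol**
- 32 participants per experiment.
- Distance task: 2 staircases per eye-by-location cell, at least 30 trials each, and two runs (read as one per hemifield). This gives 2 × 30 × 2 = 120 trials per cell per person, and 120 × 4 × 32 = 15,360 trials in all.
- Area task: 50 adjustments per eye, location and hemifield, so 100 per cell per person.
- Criterion p < 0.05, taken as two-sided because sidedness is not stated.

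**Assumptions**
- Between-person SD of the location effect on bias (τ): not in the documents, varied from 0 to 0.5.
- Psychometric SD of 1 DVA, so probit units equal DVA.
- Probit information of 0.55 per trial, used in the formula only.

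**Formula.** Let v be the trial-noise variance of one person's location contrast in one eye. The random-intercept model uses v, but the true variance is v + τ². The actual error rate is therefore 2 × [1 − Φ(1.96 / √(1 + τ²/v))].

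**Distance task.** v = 2 / (120 × 0.55) = 0.0303. At τ = 0.10 the ratio is 1 + 0.01/0.0303 = 1.33 and the rate is 2 × [1 − Φ(1.96/1.153)] = 8.9%. The simulated columns use the protocol's 0.5 DVA staircases with 30 trials each (10-reversal rule not simulated), participant-by-hemifield intercepts and 250 runs per row. Monte Carlo error is about 1.4 points at a 5% rate.

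| τ (DVA) | 1 + τ²/v | Formula | Simulated, intercepts only | Simulated, participant-level t-test |
|---|---|---|---|---|
| 0 | 1.00 | 5.0% | 4.0% | 6.8% |
| 0.10 | 1.33 | 8.9% | 10.4% | 6.8% |
| 0.20 | 2.32 | 19.8% | 15.6% | 3.2% |
| 0.30 | 3.97 | 32.5% | 24.8% | 4.0% |
| 0.50 | 9.25 | 51.9% | 40.0% | 2.4% |

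The eye-by-location interaction behaves alike: 4.8%, 10.0%, 17.2%, 28.4% and 40.4%.

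A second simulation (400–500 runs, no hemifield differences) gave 3.7–5.6% at 0, 9.0% at 0.10, 12.4% at 0.15, 20.0% at 0.25 and 42.2% at 0.50. Participant-clustered tests gave 3.7–6.2%. A further rerun gave 6%, 9% and 21% at 0, 0.10 and 0.25.

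The mechanism shows in the standard errors. At 0.25 the mean model standard error was 0.033 against an empirical SD of 0.052, a ratio of 1.58. Then 2 × [1 − Φ(1.96/1.58)] is about 21%, in line with the simulated rate.

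The formula runs above the simulation at larger τ. Part of the reason is that 0.55 is generous: the simulated model standard error of 0.0334 implies v = 32 × 0.0334² = 0.0357. The simulated rates are the ones to use.

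**Area task.** v = 2/100 = 0.02, with τ in units of the trial SD. Formula (simulated, 2,000 runs): 5.0% (5.6%) at 0, 6.5% (6.6%) at 0.05, 11.0% (11.0%) at 0.1, 25.8% (24.0%) at 0.2, 40.3% (40.0%) at 0.3 and 59.4% (57.1%) at 0.5. Participant-level tests gave 4.0–5.4%.

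The motion task has the same staircase structure but was not simulated.

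**The case against.** **The model is only a first estimate.** This is largely fair. The article assigns final arbitration to the Bayesian comparison, and no passage lets a first-stage p-value decide between theories. The hierarchy of the Bayesian models is not described. A reader might infer that the theory comparison itself is invalid, but the documents do not show that those models share the gap. The objection does not remove the fault: the Discussion still makes the mixed model the first assessment and ties NREP's small effect to p < 0.05.

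**Further random terms may be specified elsewhere.** The wording is not exhaustive, and the article points to a preregistration. But the only random terms stated are intercepts, and the claim about participant variability is attached to those terms.

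**The size is assumed.** This stands. A reader might infer that false positives will be common, but nothing in the documents favours an SD of 0.25–0.50 over 0.05–0.10. At SD 0 there is no inflation.

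**Not every false positive helps IIT or NREP.** This also stands. Both predict only a decrease, and the Discussion treats perceived enlargement as an unexpected finding. About half the rejections could count for them, roughly 10% at SD 0.25. NREP also allows no change, so a spurious small decrease gains it nothing over a null.

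**Precision tests.** A reader might infer that slope tests suffer at least as badly, but the simulations do not support a figure. With between-person SDs of 0.2–0.3 in log sigma placed at one location only, rejection was 19–28% in a rerun, nearly all in one direction. Unequal heterogeneity attenuates the pooled slope and so shifts its mean. Spread evenly over locations, the rate fell to 9–11%. The large slope rates are thus mostly attenuation bias, not too small a standard error.

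**Conclusion.** The concern holds as a fault of model structure. As written, the first-stage model assumes identical location and eye effects in every participant and tests them against trial noise. For bias in the distance task, the nominal 5% two-sided test rejects a true null about 5% of the time at a between-person SD of 0, 9–10% at 0.10, about 20% at 0.25 and about 40% at 0.50 DVA. The area task follows a similar course in units of its trial SD. These rates rest on the assumed SDs and, in the distance task, on a psychometric SD of 1 DVA. Nesting hemifield within participant does not remove the inflation, because the tabulated simulation already had participant-by-hemifield intercepts. For precision the structural gap is the same, but its size is not established.

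**What to change.** In Planned analyses and expected outcomes, add by-participant random effects for location, eye and location × eye on bias, and for the stimulus slope and its interactions with these conditions. They can be made uncorrelated if convergence requires it.

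Alternatively, estimate each participant's point of subjective equality and log sigma in each cell, then run paired contrasts across the 32 participants (31 degrees of freedom). Name this two-stage analysis as the fallback if the full model does not converge, so that the analysis does not revert to random intercepts alone. If the Bayesian models do not already have participant-level effects, give them the same structure.

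The cost is a change of wording and code before the final analysis, wider intervals and some convergence work. No new data are needed.

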### Data management and sharing plan

The management of intellectual property of study protocols in the adversarial collaboration, including the present one, will align with the European Commission and the guidelines of both institutions involved in the project, as will our policy for sharing behavioural, and eye tracking data. Specifically, we will adhere to the European Commission’s open access and data management policy and the European Commission’s Grants Policy on sharing of unique research resources.

All investigators agree to willingly share data and materials associated with this project so as to expedite future discoveries in consciousness and maximise the study’s impact. Following the acquisition of data, all data and any subsequent analysis will be uploaded to a shared server (EBRAINS, https://www.ebrains.eu/) available to all team members, as well as all members of the consortium and its associated committees. Over the life of the project, analysis and findings based on these data will be shared through multiple media, such as (including but not limited to) media appearance, lab meetings, conference talks and posters, and seminars (both at the host institutes and with the broader national and international scientific community).

In line with the principles of open science, de-identified data will be made available on an appropriate data repository. The specific items to be made publicly available as part of our resource sharing plan include:

All code used for stimulus creation, manipulation, and experiment presentation, as well as all code used to pre-process or analyse the data.All (de-identified) eye-tracking, and behavioural data adhering to FAIR data principles. Despite creating no neuroimaging data in this project the larger TWCF ARC project will require the organisation of all raw data and derivatives to align with the Brain Imaging Data Structure BIDS format (http://bids.neuroimaging.io). All metadata will be made available.Any peer-reviewed publication (the TWCF ARC project requires open access publications).

To allow the reuse of data—whilst also ensuring its integrity—downloading parties will be required to register before downloading any demographic, behavioural, eye tracking, or physiological data. A condition of the registration is that users agree: 1) not to distribute the data to third parties; 2) not to attempt to identify study participants; 3) to properly acknowledge the data resources. Data will be converted to shareable data formats (BIDS) and machine-readable annotations of the task and R/Matlab/Python scripts detailing the purpose of components will be included. There will be a GITHUB repository linked to the primary EBRAINS (or an equivalent alternative) repository that will be made available at the completion of the larger INTREPID project. We will review all data prior to upload to ensure they do not contain personal information or identifiable features. Data will be stripped of these details and will be General Data Protection Regulation (GDPR) compliant. We will share unprocessed (ASCII), minimally processed and final processed (CSV) data. All custom code and analysis pipelines will be shared. The experiment will be made available following publication via the OSF platform which links the user with all data being shared via EBRAINS (https://ebrains.eu/).

## Discussion

This study protocol forms one of four protocols (to be published separately) that were designed in an adversarial collaboration (Intrepid project) between information integration theory (IIT; [5]), and two branches of predictive processing, active inference (AI; [6,7]) and neurorepresentationalism (NREP; [8,9,15]). In the context of our study, the theories made differential predictions on the behavioural effects that the un-stimulated blind spot region may have on judgements of distance, area, and motion curvature. We will use these behavioural effects to assess the different theoretical predictions of the three theories (see Fig 6 for simulated data of each theory’s predictions). This will be done first through standard linear mixed-effects modelling, followed by a Bayesian analysis applied both within our protocol and across the broader collaborative framework, aiming to better understand the mechanisms behind the conscious experience of space.

Among the challenges that may affect our ability to arbitrate between the theoretical accounts and our observed data is, firstly, the fact that although the different theories predicted the direction of the effect on space, they did not specify the magnitude. For example, NREP argued that ‘small’ (down to ‘non-existent’) spatial disruptions could take place when judgements involved the un-stimulated blind spot region, where ‘small’ means a modest effect that is nonetheless significant (p < 0.05 according to frequentist statistics). Conversely, IIT proposed that space should be perceived as smaller around the blind spot region, but did not define how much of a disruption would be theoretically relevant.

A second outcome that could affect our arbitration is one in which we find an effect that was not predicted by any theory. For instance, we could find that space nearing the blind spot is perceived to be larger and not smaller (i.e., differing from IIT’s prediction), or that judgement precision around the blind spot location is affected for the contralateral eye and not the ipsilateral eye (i.e., differing from IIT’s and AI prediction). In this case, there may not be a straightforward explanation from any specific theory, but unexpected findings would still be valuable and could be used to further the frameworks’ future predictions. Another possibility is that different theories are supported by different experimental results (e.g., IIT supported by the distance task, NREP by the area task and AI by the motion curvature task), implying that the different theories are better fitted to explain different types of spatial judgements. In such scenarios, the results will be taken to refine or modify theories so that they may come to better explain non-confirmed results.

### The adversarial collaboration setting for this study

This study protocol forms part of a consortium project (Intrepid) engaged in adversarial collaboration among theories of consciousness, in this particular case IIT, NREP and AI (https://doi.org/10.54224/20646). In this consortium project, our experiment was specifically designed to test IIT’s prediction that differences in connectivity should lead to spatial distortions even in the absence of neural activity. As such, the results from this experiment are most informative with respect to IIT. Other experiments within the consortium were designed with different theoretical emphases and will therefore be most informative in those contexts.

The results for the basic predictions described above, as well as the results from the other experiments in this adversarial collaboration, will be analysed according to the Bayesian Adversarial Collaboration model comparison analysis scheme set out in [30], where all predictions from the theory leads are registered in protocols and at the OSF site. This Bayesian analysis will then be informative for further interpretation and discussion of the overall outcomes of the consortium’s findings. Other statistical tests (e.g., classical frequentist) may be conducted to further analyse the data, and analyses will be cross-validated by replication labs, primary labs and the teams of theory leads.

The proposed Bayesian Adversarial Collaboration model comparison analysis scheme is an evidence accumulation approach (see [30], for an in-depth discussion of its advantages over alternative approaches such as falsification). Our results should therefore be interpreted as contributing evidence toward the theory whose predictions best explain whether spatial distortions arise in the presence of the blind spot, with particular relevance for evaluating IIT’s claims.

### Dissemination plans

The outcomes of this experimental protocol and of the other experimental protocols in the Adversarial Collaboration will likely be published as a stand-alone article in the first instance or might be published as one combined paper. Each of these experiments and their components may or may not be presented through posters and talks at both international and regional conferences.

Following the completion and publication of the experiments described in each of the protocols published by the respective experimental groups, an integrative paper will be published that brings together and discusses the overall results in the context of the Adversarial Collaboration; a Bayesian analysis along the lines of [30] may follow or precede this paper.

Finally, the Intrepid Consortium plans to deliver public talks and a symposium to present and discuss the outcomes of the entire adversarial collaboration.

